**Sample size calculation**

The sample size calculation for the study has been performed using G*Power Software. An F-test was selected for an ANOVA with repeated measures, accounting for within-between interaction. Input parameters included a medium effect size f=0.20, a significance level of 0.05, a power of 0.8, four groups, five measurements, and a nonsphericity correction of 1. The results indicated that a total sample size of 48 participants is required to achieve the sufficient statistical power. To account for potential losses of 10%, the sample size will be increased to 52 participants (13 per group) to compensate for possible dropouts.

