***Protocol for Transcranial and Peripheral Electromagnetic Stimulation in the Study***

Control (Cont) Group: The electromagnetic stimulation machine will be positioned identically as in the active treatment groups. However, the machine will be turned off, and pre-recorded sounds of the machine's operation will be playing during the treatment session.

Super Inductive (P) Group: The PES treatment will be administered, following the Long-Term Potentiation protocol. This protocol will entail five stimulations at 100 Hz, each lasting for 5 seconds, interspersed with 55-second rest intervals. The total stimulation time for this group will be 10 minutes.

Transcranial Stimulation (T) Group: This group will receive TES treatment involving 2000 pulses administered over a minimum duration of 20 minutes, targeting the cortical area M1.

Combined Stimulation (Comb) Group: Participants in this group will receive a combination of both PES and TES treatments, with the total stimulation time extending to 30 minutes.

In all groups, the treatment will start one hour post the eccentric exercise session, aligning with the onset of fatigue, time T2 in the study.

The TES and PES treatments will be administered using a MagRex magnetic stimulator equipped with a ring-shaped coil / 8-shaped coil (MR Inc., Republic of Korea, http://www.mrev.co.kr).

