**Statistical analysis**

SPSS v.29 (IBM, Armonk, NY, USA) will be used to perform statistical analysis. Normal distribution of data will be assessed using histograms and the Shapiro-Wilk test. Variables with a p-value less than <0.05 will be considered to have a non-normal distribution, while variables with a p-value greater than 0.05 will be considered to have a normal distribution. To describe the sample, the mean and standard deviation will be reported for normally distributed variables, while the median and interquartile range will be reported for non-normally distributed variables. Independent t tests or Mann-Whitney U tests will be used to compare means between groups at baseline for quantitative variables. When the assumptions are met, a 5x4 (5 measurements x 4 groups) mixed analysis of variance (ANOVA) will be performed, with correction for multiple comparisons using the Bonferroni test. The effect size, expressed as partial eta squared (ηp2​), can be categorized into three ranges: a small effect (0.01), a medium effect (0.06), and a large effect (0.14).

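### T1 is used as an outcome level instead of a covariate, and the Bonferroni comparisons that follow, with no stated family, are mostly weak tests of which stimulation works

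*Protocol*

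**What the plan says.** The Statistical analysis section states that "a 5x4 (5 measurements x 4 groups) mixed analysis of variance (ANOVA) will be performed", "with correction for multiple comparisons using the Bonferroni test". The five measurements are T1 to T5, so T1 is a level of the outcome. T1 has one other use: "Independent t tests or Mann-Whitney U tests will be used to compare means between groups at baseline for quantitative variables". It is not used to adjust later values.

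The section does not name the pairs or visits to be compared, the Bonferroni divisor, or whether pairwise tests wait for a significant interaction.

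The Sample size calculation section covers the omnibus test only: "An F-test was selected for an ANOVA with repeated measures, accounting for within-between interaction". Its inputs are "a medium effect size f=0.20, a significance level of 0.05, a power of 0.8, four groups, five measurements, and a nonsphericity correction of 1".

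The Procedure section places T1 before the exercise and T2 to T5 at 1, 24, 48 and 72 hours after it. The stimulation section says that "the treatment will start one hour post the eccentric exercise session, aligning with the onset of fatigue, time T2 in the study". It does not say whether the T2 assessment comes before or after the treatment.

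**The concern.** A significant group-by-time interaction on 12 degrees of freedom does not say which of the three active arms differs from control, or when. That conclusion must come from the pairwise comparisons, which were not sized.

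T1 cannot show a treatment effect, and T2 may not. Comparisons there spend part of the error allowance, while the T1 value, which could reduce the noise at later visits, is not used for that purpose.

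The open divisor matters too. The stricter choice detects little. The looser one, read without a preceding overall test, does not hold 5% across visits. A choice made after seeing the data could change the conclusion.

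**Working it through.** **Inputs from the protocol.** Four arms, five measurements, f=0.20, alpha 0.05, power 0.80, nonsphericity correction 1, 48 required, 52 enrolled (13 per arm).

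**Assumptions, not in the protocol.** Correlation between visits (rho) 0.5, varied where shown; a pairwise difference of 0.8 SD; 13 completers per arm.

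**1. The protocol's own figure.** Noncentrality = f² × N × m / (1 − rho). At N=48: 0.04 × 48 × 5 / 0.5 = 19.2, with 12 and (48 − 4) × 4 = 176 degrees of freedom. Power is 0.775 at N=44, 0.821 at 48 and 0.860 at 52. The stated 48 is therefore reproduced at rho 0.5, for the interaction test alone.

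**2. Number of possible tests.** Four arms give 4 × 3 / 2 = 6 pairs; over five visits, 6 × 5 = 30.

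**3. Power for one pair at one visit.** Two-sided noncentral t with noncentrality d × √(n/2) = 0.8 × √6.5 = 2.04, on 4 × 13 − 4 = 48 degrees of freedom. Any false difference when no arm differs was simulated at rho 0.5.

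| Rule | Power at 0.8 SD | Any false pairwise difference |
|---|---|---|
| 0.05/6 within each of five visits, no overall test first | 25.1% | 15.7% to 16.0% |
| The same, only after a significant interaction | not computed | about 2% |
| 0.05/30 | 11.4% | 3.8% |

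The first row's error is 18.6% at rho 0 and 8.8% at rho 0.9. The 25% and the 16% belong to the same rule; the 11% goes with controlled error.

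**4. Differences implied by f=0.20.** The largest pairwise difference is √(0.04 / (variance of arm pattern × variance of time pattern)), in SD units.
- Two arms against two, effect at T3 to T5: √(0.04 / (0.25 × 0.24)) = 0.82.
- Graded arms (0, 0.5, 0.5, 1), effect at T2 to T5: √(0.04 / (0.125 × 0.16)) = 1.41.

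Over this range, power for that pair is 26% to 80% with divisor 6 and 12% to 61% with divisor 30.

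**5. T1 as covariate, with Holm.** Adjustment multiplies the residual SD by √(1 − rho²), so 0.8 SD acts like 0.8/√(1 − rho²) = 0.84, 0.92 or 1.12 SD at rho 0.3, 0.5 or 0.7. Simulated power for a control pair at one visit, with all three active arms 0.8 SD above control and Holm over six pairs, is 29%, 37% and 56%, against about 25% as planned. Most of the gain comes from T1. These figures do not include any loss from requiring a significant overall test first.

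**6. A summary contrast.** For the T1-adjusted mean of T3 to T5 with Holm, power is about 69% if 0.8 SD holds at all three visits, and about 5% if it is present at one visit only (against about 24% for the comparison at that visit).

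**The case against.** - **The family is not fixed by the protocol.** A reader might infer that Bonferroni covers all 30 tests, T1 included. The text does not say so. Six pairs on overall means, control pairs only, or pairs read after the interaction are all open, and a statistical analysis plan that is not shown may define the family. This stands, so the silence alone is not the finding. The finding is the method that the protocol does state: T1 as an outcome level, with Bonferroni.
- **The 16% is an unfavourable reading.** It needs pairwise tests at all five visits without a preceding overall test. The trial is sized for the interaction, so reading pairs only after it is at least as natural, and the figure is then about 2%. This stands.
- **0.8 SD is an assumption just below the low end of what f=0.20 implies.** This stands, and is why the range of 26% to 80% or 12% to 61% is shown.
- **One visit is a narrow target.** The chance of detecting a given control pair at one or more of T3 to T5 is about 46% (divisor 6) or 24% (divisor 30). This is fair, but still well short of 80%.
- **T1 costs little as a test.** Dropping it from a single family moves power only from 11.4% (30 tests) to 12.8% (24 tests), and per-visit error from 16% to 13%. This is correct. The loss lies mainly in not adjusting for T1.
- **Averaging T3 to T5 would replace the trial's question.** The visits are meant to follow recovery over time, and the mean nearly loses an effect confined to one visit. This stands against making the mean the sole comparison.

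**Conclusion.** The concern holds in a limited form. The stated analysis treats a pre-treatment measurement as an outcome and follows it with Bonferroni comparisons that were not sized. At divisor 30, power for the largest pair stays below 80% for every effect pattern examined under f=0.20; at divisor 6, only the most favourable pattern reaches about 80%. These figures rest on 13 completers per arm and on rho 0.5 for the reading of f=0.20.

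The documents do not support saying that the plan has 11% to 25% power, or that it has a 16% error rate. Both depend on an assumed effect and on one reading of an open sentence. Nor are low power and inflated error two alternatives: under the per-visit rule without an overall test, they occur together.

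This should be changed. It is a matter of analysis efficiency and clarity, and it needs no further recruitment.

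**What to change.** In the Statistical analysis section:
1. Use T1 as a covariate and remove it from the outcome levels.
2. Compare arms at post-treatment visits only. State whether T2 is assessed before or after treatment starts, and exclude it from the comparisons if before.
3. Read pairwise tests only after a significant overall test of the arms. A false pair then needs a false overall result first, so error stays at or below 5% when no arm differs.
4. Adjust the six pairwise p values by Holm in place of Bonferroni, and state that this is done within each visit.

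The T1-adjusted mean of T3 to T5 may be added as one prespecified summary contrast. It should not replace the visit comparisons unless the sponsor justifies expecting an effect sustained over those visits.

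**Cost.** A slightly longer analysis text, and Holm worked outside the default output. Because "a total sample size of 48 participants is required to achieve the sufficient statistical power" refers to the interaction over five outcome levels, the sample-size paragraph should be checked against the revised overall test. No extra participants or measurements are needed to adopt the change.

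### The partial eta squared bands can grade a null group-by-time interaction as 'medium' in 51% of trials with 48 men analysed, or 43% with 52

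*Protocol*

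**What the plan says.** The Statistical analysis section plans that "a 5x4 (5 measurements x 4 groups) mixed analysis of variance (ANOVA) will be performed", with Bonferroni correction for multiple comparisons. It continues: "The effect size, expressed as partial eta squared", which "can be categorized into three ranges: a small effect (0.01), a medium effect (0.06), and a large effect (0.14"). No other effect-size measure is named, no bias-adjusted version is mentioned, and nothing limits the labels to significant terms or to particular terms of the model.

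The Sample size calculation section shows which term the trial was sized for: "An F-test was selected for an ANOVA with repeated measures, accounting for within-between interaction". The inputs are "a medium effect size f=0.20, a significance level of 0.05, a power of 0.8", with "four groups, five measurements, and a nonsphericity correction of 1". The result is that "a total sample size of 48 participants is required", and for losses "the sample size will be increased to 52 participants (13 per group").

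**The concern.** Sample partial eta squared is the effect sum of squares divided by the sum of the effect and error sums of squares. It cannot be negative, so it is above zero even when nothing is happening. Its average under no effect is df_effect / (df_effect + df_error). With many numerator df and few participants that floor is not negligible, and in this design it falls almost exactly on the 0.06 benchmark.

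The bands are meant to help a reader judge how much the stimulation did. If no effect at all commonly earns the middle label, the scale cannot do that for the terms that carry treatment information. The practical risk is a report pairing a non-significant interaction with a 'medium' effect, read as promise that a small trial narrowly missed. The Protocol lists several outcomes (surface EMG, dynamometry, jump, CK, lactate), so there are several chances for that to happen.

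**Working it through.** **Inputs.** From the Protocol: 4 groups, 5 measurements, nonsphericity correction 1, f = 0.20, alpha 0.05, power 0.80, 48 required and 52 to recruit; benchmarks 0.01, 0.06 and 0.14. Assumed: a correlation of 0.5 between measurements. The Protocol gives none, and it is needed only for the first step.

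**1. The plan's own figure.** Interaction df = (4−1)(5−1) = 12; error df = 4(N−4). With noncentrality λ = f²·N·5/(1−0.5), power is 0.799 at N = 46, 0.810 at 47 and 0.821 at 48. The stated 48 is the first multiple of four to reach 0.80. This confirms that the 12-df interaction is the term the trial was sized on.

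**2. Null distribution for the interaction.** With no interaction and sphericity, partial eta squared follows Beta(df_effect/2, df_error/2). For N = 48, error df = 4 × 44 = 176, giving Beta(6, 88). For N = 52, error df = 4 × 48 = 192, giving Beta(6, 96).

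| No true interaction | N = 48 | N = 52 |
|---|---|---|
| Mean | 12/188 = 0.064 | 12/204 = 0.059 |
| Median | 0.061 | 0.056 |
| P(≥ 0.01) | 99.96% | 99.94% |
| P(≥ 0.06) | 51.2% | 43.1% |
| P(≥ 0.14) | 0.7% | 0.3% |

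At N = 50 the mean is 0.061 and P(≥ 0.06) is 47%. The 0.01 row reads the listed values as lower cut-offs, which the Protocol does not say outright.

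**3. Relation to the F-test.** The critical value F(12, 176) = 1.808 corresponds to 12 × 1.808 / (12 × 1.808 + 176) = 0.110. F(12, 192) = 1.803 corresponds to 0.101. An observed 0.06 has p = 0.51 at N = 48 and p = 0.43 at N = 52. Both critical values exceed 0.06, so every significant null result is also at or above 0.06. The share that is at least 'medium' yet non-significant is therefore 51.2 − 5.0 = 46% or 43.1 − 5.0 = 38%.

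**4. Other terms.** Group main effect, 3 and N−4 df: Beta(1.5, 22) or Beta(1.5, 24), mean 3/47 = 0.064 or 3/51 = 0.059, P(≥ 0.06) = 43% or 39%. Time effect, 4 and 4(N−4) df: mean 4/180 = 0.022 or 4/196 = 0.020, P(≥ 0.06) = 2.7% or 1.8%.

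**5. Robustness.** In 20,000 simulated null trials per setting, compound symmetry gave P(≥ 0.06) = 51.5% and 42.9% for the interaction. Serial correlation of 0.7, which breaks sphericity, gave 48.2% and 41.3%.

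**6. The corrected measure.** Partial epsilon squared = (SS_effect − df_effect × MS_error) / (SS_effect + SS_error) = η² − (df_effect/df_error)(1 − η²). Putting in the null mean of η² gives exactly 0. Reaching 0.06 requires η² ≥ (0.06 + 12/176)/(1 + 12/176) = 0.120 at N = 48, or (0.06 + 12/192)/(1 + 12/192) = 0.115 at N = 52. For the interaction this has null probability 2.7% or 2.0%. For the group term the thresholds are the same (3/44 = 12/176 and 3/48 = 12/192), but the Beta(1.5, 22) and Beta(1.5, 24) tails give 13% and 11%. The correction removes the bias there but leaves more sampling noise.

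**The case against.** The benchmarks are conventional and are not misquoted. The Protocol says effects *can* be placed in these bands, which is a key for description and not a decision rule. Inference rests on the mixed ANOVA with Bonferroni correction, and that test is unaffected. A null interaction sitting at 0.06 would appear beside a p-value of 0.4 to 0.5. All of this stands.

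A reader might therefore infer too much in four ways:

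- *That the plan leads to a wrong conclusion about efficacy about half the time.* It does not. No treatment is declared effective or promising because of its band, and the harm needs someone to read the label without the p-value.
- *That the trial will report small or medium effects for nearly every null outcome.* The Protocol does not say which terms are labelled, or that non-significant terms are. It permits this without prescribing it.
- *That no effect always averages above the middle benchmark, whatever the term.* With all 52 analysed, the interaction's null mean (0.059) and median (0.056) lie just below 0.06. The time effect is hardly touched, and a null interaction almost never reaches 0.14.
- *That missing mean differences and intervals are themselves an error.* Such reporting may sit in an analysis plan that is not shown, and an omnibus measure is not wrong for lacking direction.

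What remains is that the Protocol does fix this measure and these bands, names no alternative, and does not tie the label to significance. For both terms that carry treatment information, the scale starts at about its own middle mark.

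**Conclusion.** The point holds as a fault in a stated effect-size grading, not in the hypothesis test or the sample size. With no true effect, the uncorrected interaction value reaches 'medium' in 51% (48 analysed) to 43% (52 analysed) of trials, and does so without significance in 46% to 38%. The group main effect is affected to a similar degree; the time effect is not. The exact figures assume normal errors and, for the interaction and time terms, sphericity. Strong serial correlation lowers the interaction figures by only two or three percentage points. The correction is worth making because the rule is already written down and is nearly free to change.

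**What to change.** In the Statistical analysis section:

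1. For the group-by-time and group terms, replace uncorrected partial eta squared with partial epsilon squared (formula above) or partial omega squared, with a confidence interval.
2. State that the 0.01/0.06/0.14 labels are not applied to the uncorrected value or to non-significant terms. The second condition matters most for the group term, where the corrected value still reaches 0.06 by chance in 13% or 11% of null trials. Removing every verbal label would go further than the bias requires.
3. Base interpretation on the between-arm differences at each post-treatment visit, in the outcome's units, with 95% confidence intervals from the same model.

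The cost is a few sentences of analysis wording. No new data, design change or different model is needed. The downside is that reported effect sizes will be smaller, and partial epsilon squared will sometimes be negative.
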